#### Budget impact analysis (BIA)

A BIA will be performed using the ZonMw BIA tool to estimate the financial impact of different implementation scenarios at the national level. The analysis will be based on the costs as estimated during the study and the expected number of patients in the Netherlands. The BIA will be conducted from the perspectives of society, the hospital and ‘Budgettair Kader Zorg’ (translates to ‘budgetary framework for healthcare’), with the appropriate prices and charges. Costs will be estimated per budget period (1 year) for a time horizon of 5 years, assuming 50%–100% implementation after 4 years.

### Benefits and risk assessment, group relatedness

The additional risks of performing TMR during an amputation are negligible. TMR can be performed at any level of the lower extremity with a standardised technique. For TMR to be possible in transfemoral and through-knee amputations, an additional sham incision (around 10 cm) must be made on the dorsal side of the leg, medial to the sartorius muscle. To properly blind study participants, this additional incision must also be superficially performed for the transfemoral and through-knee amputations in the control group. In our experience, this will not result in increased postoperative pain or difficulty sitting.

The surgery time for a standard transtibial and transfemoral amputation will be 45–90 min, depending on the surgeon’s experience. The TMR procedure will add 30–90 min to the surgery.^17^ This extra time investment will rely on technical aspects related to the level of amputation and the surgeon’s experience. Although an increase in surgical time of this length is related to a slightly higher risk of infection, Deeyor *et al*^18^ did not find more complications in patients who had acute TMR compared with the standard of care. Deeyor *et al* found a 77% complication rate in the primary TMR group, compared with 87% in the amputation-only group.^18^ There is a small chance of failure of the TMR procedure.^40^ If patients suffer harm from trial participation, the LUMC provides participant insurance for potential financial compensation.

The burden of the study is acceptable, as participation only requires patients to complete several questionnaires at five evaluation time points. This will translate to about 2 min at 2 weeks, 14–21 min at 3, 6 and 9 months and 20–29 min at 12 months postamputation. Additionally, participants will fill out a daily questionnaire consisting of 2 questions about pain for 30 consecutive days at 11 months postamputation. Patients who fail to complete the questionnaires in 2 weeks will receive an automatic reminder and a call from the researcher to promote participant retention.

Depending on the literature source and the level of amputation, the frequency of PAP ranges between 33% and 86%.^3^ In the patient series performed on primary TMR, PAP was present in 8%–29%.^1719^,^22^ After primary TMR, 90.9% of patients who had TMR were ambulatory compared with 70.5% (p<0.01) in the amputation-only group. O’Brien *et al* showed a longitudinal durability of this effect over 18 months or more in 81 patients.^23^ One trial on TMR as a secondary procedure^14^ showed an average decrease in pain NRS of 3.2 in the TMR arm compared with an average increase of 0.2 in the standard treatment arm. Various cohort studies on secondary TMR show similar results.

Primary TMR results in a reduction of the chance of developing PAP. The risks and the burden for patients are negligible.

Because the risks of TMR are negligible, no data safety management board has been assigned. During the study, patient safety and execution of study procedures will be closely monitored by an independent clinical trial monitor and auditor according to local regulations.

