### Study procedures

After randomisation, patients will receive general anaesthesia without a muscle relaxant for the TMR group. Intraoperative epidural anaesthesia is not allowed as this will reduce nerve conduction, making nerve stimulation less dependable. The amputation will be performed by a qualified vascular surgeon or a senior resident in training under supervision. The skin will be incised using a fishmouth incision (transfemoral and through-knee) and according to Burgess’ technique (transtibial). If patients are randomised in the TMR group, a trained nerve surgeon will perform the nerve coaptation. Postoperative protocol is similar for both interventions, including the use of analgesia. In transfemoral and through-knee amputations, there will be an additional 10-centimetre incision on the posterior side of the leg. This additional incision is necessary to coaptate the sciatic nerve. To ensure proper blinding, a sham skin incision will be performed in the control group. Closure and dressing of the wound will be similar between groups.

To ensure homogeneity in all participating centres a treatment and postoperative care protocol will be distributed for both the intervention and control groups (online supplemental file 3), in addition to a central cadaver-based TMR course.

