#### Control group

The patients in the control group will receive traction neurectomy during the major lower limb amputation, which is the current standard of care in the Netherlands, and this will reduce confounding by the length of the nerve stumps. Ligation or infiltration with a local anaesthetic or alcohol will not be allowed, as we believe this causes significantly more PAP. Amputation technique and nerve handling are carefully documented according to standardised protocols.

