#### Secondary study parameters/endpoints

Secondary endpoints include the use of analgesics or pain interventions, surgical time, length of hospital stay and adverse events or complications, including survival. In addition, multiple questionnaires will be sent to the participants regarding RLP and PLP during the study (measured by the NRS); pain behaviour and pain interference during the study (measured by the PROMIS Pain Behaviour and Pain Interference Short Forms)^29^; local, diffuse or radiating pain (measured by the Interdisciplinary Care for Amputee Network pain sketches)^30^; neuropathic pain (measured by the PainDetect)^31^; quality of life (measured by the European Quality of Life - 5 Dimensions - 5 Levels (EQ-5D-5L))^32^; anxiety and depression symptoms (measured by the Hospital Anxiety and Depression Scale)^33^; perceived treatment effect (measured by the Global Perceived Effect - Dutch Version)^34^ and mobility 1 year after surgery (measured by the Prosthetic Limb Users Survey of Mobility).^35^ A cost-effectiveness analysis (CEA; measured by the Medical Consumption Questionnaire (iMCQ))^36^ and the Productivity Cost Questionnaire (iPCQ)^37^ and a budget impact analysis (BIA) (measured by the ZonMw BIA tool) will also be performed at the end of the study. All data will be collected using validated questionnaires at different time points (table 1).

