#### Cost-effectiveness analysis (CEA)

The economic evaluation will be a trial-based cost-utility analysis (CUA) from a societal perspective (CUA, ie, costs per quality-adjusted life years (QALYs)). Care with and without TMR will be compared with a 1-year time horizon. Estimated societal costs will include hospital (based on study registrations) and other healthcare and productivity costs, using the iMCQ^36^ and iPCQ^37^ at 3, 6, 9 and 12 months. A cost-price analysis will be performed for the TMR. Other healthcare costs will be valued according to the Dutch reference prices whenever possible, including travel costs without discounting (because of the short time horizon). Productivity losses will be valued using the friction-cost method. QALYs will be calculated using the Dutch tariff for the EQ-5D-5L,^32^ at 2 weeks and at 3, 6, 9 and 12 months. Average costs and QALYs will be compared according to ITT, using net-benefit analysis and multiple imputation to account for missing data. Sensitivity analyses will include the cost perspective (healthcare instead of societal) and the utility measure (European Quality of Life visual analogue scale with power-transformation instead of the EQ-5D-5L). If, contrary to expectations, TMR does not deliver better QALYs at lower costs, mathematical extrapolation will be used to perform a threshold analysis on the time horizon.

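### In transfemoral and through-knee controls, the time, wound events and cost of the blinding-only sham incision are not separated out, so TMR's extra burden over usual care may be understated

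*Protocol article*

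**What the plan says.** Study procedures describes an additional posterior incision in transfemoral and through-knee amputations, which is needed to reach the sciatic nerve for TMR. For controls it adds: "To ensure proper blinding, a sham skin incision will be performed in the control group". The benefit and risk section gives the length ("an additional sham incision (around 10 cm) must be made on the dorsal side of the leg") and limits the control version by depth and level: "To properly blind study participants, this additional incision must also be superficially performed for the transfemoral and through-knee amputations in the control group". No such incision is described for transtibial amputations.

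The Control group section says of traction neurectomy: "which is the current standard of care in the Netherlands". The only stated consequence of the sham is a reassurance about comfort: "In our experience, this will not result in increased postoperative pain or difficulty sitting". Wound complications, operating time and cost of the sham are not discussed.

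The section Secondary study parameters/endpoints lists the endpoints concerned here in its opening sentence: "Secondary endpoints include the use of analgesics or pain interventions, surgical time, length of hospital stay and adverse events or complications, including survival". For the economic evaluation, the CEA section says: "Care with and without TMR will be compared with a 1-year time horizon". It takes hospital costs from study registrations and compares average costs and QALYs by intention to treat. It names two sensitivity analyses, on cost perspective and utility measure. The BIA section carries the costs estimated in the study to national level.

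**The concern.** A sham is the right comparator for a blinded pain score. It is not the right comparator for what a procedure adds in operating time, wound harm and money, because a patient treated outside the trial without TMR would not have the wound. In the TMR arm the posterior incision is a true part of the intervention and should count. In upper-leg controls it exists only because of the trial. When both are counted, part of TMR's burden cancels out of the difference.

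The hypothesis includes improved quality of life at lower costs, and the budget impact analysis is meant to inform national implementation. Both need the contrast with usual care. As written, the upper-leg data give TMR against usual care plus a superficial trial-only wound. Any resulting error favours TMR. Wound site and sham minutes are also hard to reconstruct later if they are not recorded at the time.

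**Working it through.** **Stated contrast and stated data**

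| Item | Stated | Consequence |
|---|---|---|
| Comparator | Traction neurectomy as Dutch standard care | No posterior wound in that care |
| What upper-leg controls receive | Traction neurectomy plus a superficial incision of about 10 cm | Extra time and a second wound |
| What transtibial controls receive | No sham described | No tilt |
| Economic contrast | Care with v without TMR | Target is usual care |
| Cost source | Study registrations, by intention to treat; the BIA uses the same costs | Sham resources enter unless removed |
| Step to separate the sham | None stated | Direction of any error is towards TMR |

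**Direction.** Let s be the share of controls at transfemoral or through-knee level and d the average increment that the sham adds in those patients (minutes, events or cost). The control mean is raised by s × d, and the measured excess of TMR over usual care is too small by the same amount. In transtibial patients d = 0.

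**Size.** The article gives neither s nor d, so the values below are assumptions. The article's own figures are the 30–90 minutes that TMR adds, the 87% complication rate after amputation alone in a cited study, and 203 patients, or about 101 per arm (203/2 = 101.5).

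| | Narrower assumptions | Wider assumptions |
|---|---|---|
| Share of controls with sham, s | 40–60% | 30–70% |
| Sham minutes, including closure | 10–15 | 5–15 |
| Risk of a sham-wound complication | 2–10% | 1–10% |
| Shift in mean surgical time | 0.40 × 10 = 4 to 0.60 × 15 = 9 min | 0.30 × 5 = 1.5 to 0.70 × 15 = 10.5 min |
| Relative to 30–90 min | 4/90 = 4% to 9/30 = 30% | 1.5/90 = 2% to 10.5/30 = 35% |
| Shift if sham-wound events simply add | 0.40 × 2 = 0.8 to 0.60 × 10 = 6 points | 0.30 × 1 = 0.3 to 0.70 × 10 = 7 points |

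The percentages for time pair the smallest shift with the longest TMR time and the largest shift with the shortest, so they are outer limits.

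**Complications counted per patient.** The categorical analysis in Secondary study parameters (χ² or Fisher, then logistic regression) works by patient. Suppose the endpoint is any complication, the 87% rate applies, and sham-wound events are independent of other events. Then only 13% of sham-wound events fall in patients who are otherwise free of complications. On the narrower assumptions the shift becomes 0.13 × 0.8 = 0.1 to 0.13 × 6 = 0.8 points. With 87% in both arms and 101 patients per arm, the standard error of the difference is √(2 × 0.87 × 0.13 / 101) = 4.7 points, so this shift would not be noticed. A wound-specific endpoint would be affected more, up to the additive figures.

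**Cost.** No unit cost or complication cost is given, so no amount can be computed.

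**The case against.** The strongest reply is that the article nowhere says sham resources are counted as standard care. That reading is an inference from the control description, the cost source and the BIA. An article may leave costing rules, case report fields and complication attribution to the full protocol or an economic plan. The list of sensitivity analyses is introduced as what they will include, so it need not be closed. A separate cost-price analysis of TMR is planned, and technique is to be documented by standardised protocols, so sham minutes and wound site may already be captured. This stands, and it limits the point to an improvement. It does not remove it: the article itself states the contrast and the data source, and on its face the two do not match at the upper-leg levels. A cost-price analysis of TMR does not by itself take sham time or sham-wound costs out of the control arm.

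The sham is also superficial and confined to two amputation levels. This stands too. A reader might infer that the whole control arm is tilted or that the safety comparison is invalid. The article does not support that, because transtibial patients form a randomised contrast with no sham.

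A reader might also infer that the statement of negligible added risk rests on the sham-affected comparison. It does not. It is given as prior rationale, with reference to earlier work.

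The parallel registry offers patients without a sham and with the same intraoperative and postoperative variables. It is useful context, but it is not randomised and omits the cost-effectiveness questionnaires.

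Finally, removing sham-wound complication costs from the main economic analysis would leave any matching QALY loss in controls and replace observed intention-to-treat costs. This is right, and that step belongs in a sensitivity analysis.

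**Conclusion.** The point holds in limited form. In transfemoral and through-knee controls, a wound made only for blinding enters the comparisons of surgical time, complications and cost, and no step is stated to separate it. TMR's extra time, wound harm and cost over usual care may therefore be understated at these levels, and the cost part carries into the BIA. The direction follows from the design; the size does not.

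Under the narrower assumptions the arm-wide shift is 4–9 minutes of surgical time. For complications it is 0.1–0.8 points for any complication per patient, or 0.8–6 points if wound events add fully. All of these depend on assumed sham shares, minutes and risks, and the true effect may be small. The co-primary pain endpoints and the sample size are unaffected. This is a cheap improvement to secondary and economic results, not an error that threatens the trial's main conclusion.

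**What to change.** - **Keep** the sham incision and the blinded pain analysis as they are.
- **Record** wound complications and re-interventions by site (stump or posterior incision), and the minutes spent making and closing the sham, if this is not already done.
- **Report** surgical time and complications by amputation level, with transtibial as the sham-free randomised contrast.
- **Add supportive analyses**: one that subtracts sham minutes from control surgical time, and one that leaves out control events confined to the sham wound. Show both beside the observed results.
- **In the CEA and BIA**, leave sham theatre time out of control costs as protocol-driven. Add a sensitivity analysis that also removes the cost of treating sham-wound complications, stating that any matching QALY loss remains in the control arm. Show the observed intention-to-treat results alongside.

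The cost is two data fields and a few extra analyses. The drawbacks are some judgement in attributing events to the sham wound, made by staff who may know the allocation, and possibly a slightly less favourable cost result for TMR.

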### Ethics and dissemination

The local medical ethics committee of Leiden The Hague Delft approved the study (reference number P24.073). Protocol amendments and adverse events during the study will be reported and evaluated by the local ethics committee and communicated with the participating centres if needed. Before randomising patients, an informed consent form must be signed.

The results of the study will be presented at both international and national conferences and published in peer-reviewed journals. Moreover, results will also be disseminated to the public using the Dutch patient association for amputees, ‘KorterMaarKrachtig’.

### Patient and public involvement

The Dutch patient association for patients with an amputation, ‘KorterMaarKrachtig’, was involved in the development of the study. The primary outcome measures were discussed and jointly decided. Also, they assisted with the development of patient information. Together, we developed intelligible patient information and provided participants with understandable information about the goals, methodology and the potential risks and benefits of the trial.

To inform patients about the developments during the trial, we will provide updates two times a year in their journal, present at patient days and provide access to the study results once available. Moreover, the results will be discussed with the patient association, and they will be involved in further research plans on this subject and the implementation of this technique in common practice.
